#### Resident-reported outcome measures

QoL in residents without cognitive impairment will be assessed with the WHO - Five Well-being Index [34] and QUALIDEM [35] for residents with dementia. The German version of the WHO - Five Well-Being Index questionnaire published by the WHO in 1998 will be used. Scores range from 5 (all the time) to 0 (never) for a total of five items. Simple questions will be asked regarding well-being in the previous two weeks (e.g., “In the last two weeks … I was happy” or “… I was relaxed”). The sum scores range from 0 (indicating the lowest well-being) to 25 (indicating the highest well-being). A cutoff score of not more or equal than 13 is recommended.

The QUALIDEM assessment is a dementia-specific QoL instrument that is carried out by the nursing staff and that allows a proxy-based QoL rating in all stages of dementia. The German version of the QUALIDEM (version 2.0) published in 2015 will be used to assess the QoL of the resident of the previous seven days [35]. If the resident is affected by a mild to severe dementia, the 37-item assessment will be used. For residents with very severe dementia the 18-item instrument will be used. To assess whether the resident is affected by mild to severe dementia or very severe dementia, the global deterioration scale (GDS) will be used [36]. GDS scores from 2 to 6 indicate a mild to severe dementia, and the 37-item assessment of the QUALIDEM tool will be used. A GDS score of 7 indicates very severe dementia, and the 18-item QUALIDEM tool will be used.

Itch will be assessed with the 5-D Itch scale [37]. The score of the 5-D Itch scale ranges from 5 (no pruritus) to 25 (most severe pruritus) and contains five items measuring pruritus over the previous two weeks. Pain will be assessed with a numeric rating scale by residents without cognitive impairments and with a verbal rating scale by residents with cognitive impairments [38].

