### Randomization and recruitment

A 1:1 simple random generation of the allocation sequence of nursing homes to intervention (*n* = 10) or control group (*n* = 10) will be undertaken by an independent data manager via a computer-generated random list. The allocation will be conducted by the investigator using numbered opaque envelopes (1 to 20) containing computer-generated random numbers.

Nursing homes will be randomly selected from a comprehensive list of all nursing homes in Berlin (*n* = 288). Potentially eligible nursing homes will be contacted and invited to participate by letter. If there is no response by a defined deadline, the next randomly selected nursing home will be invited. If applicable, baseline characteristics (e.g., number of beds) of non-responders and reasons for non-participation will be listed in order to estimate a possible selection bias. In the case of small institutions with fewer than 70 beds/residents, the next randomly selected institution will be invited.

Recruitment of the nursing home residents and baseline measurements will be completed prior to random allocation of the nursing homes. Posters and flyers will be placed in public areas in the nursing homes to inform residents and relatives as a first step. The recruitment onsite the nursing homes will be carried out in close cooperation with a nominated key project leader of the participating nursing home. The key project leader will inform possible residents and hand out information leaflets or letters. Interested residents or their legal representatives will be contacted by the study team personally and will be invited to participate in the study.

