### Sample size calculation

Because the trial is exploratory in nature, a primary outcome is not defined. The sample size is determined such that the power of statistical tests is sufficiently high for each of several binary and continuous outcomes under realistic assumptions. According to the federal state government, there are 288 nursing homes in Berlin. According to the latest statistics (2015), the total number of nursing home residents in Berlin is 28,299. Given a mean of 100 residents per institution and a participation rate of 25%, the expected total number of residents is 25 per participating institution (500 in total). Taking into account a drop - out rate of 8%, each participating nursing home contributes about 23 residents to the trial. If m = 10 nursing homes are included in each study arm and given an ICC of ρ = 0.02 [41] and an incidence for the skin conditions of around p_C_ = 50% per annum (p.a.) (29.3% in 6 months) in the control group, the two-sided Z-test for difference in proportions at a level of α = 0.05 has a power of more than 80% if in the experimental group skin condition worsens in less than p_E_ = 29.8% p.a. (16.2% in 6 months). The power calculation for the clustered binary outcome was carried out using the method described in Ahn et al. [42]. For metrical outcomes such as the ODS score, the two-sided t-test can detect a minimal effect size (Cohen’s d) of d = 0.33 with a power of 80% at a significance level of α = 0.05. Again, an ICC of ρ = 0.02 is assumed. Therefore, the detectable effect sizes are relatively small for all outcomes. Since the effects of the experimental skin care regimen are expected to be larger, the study is not underpowered for each variable.

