## Discussion

To the best of our knowledge, this is the first trial implementing a comprehensive evidence-based skin care and prevention strategy in institutional long-term care. The skin care and prevention strategy was developed systematically, taking currently available evidence and expert opinion into account. Given the novelty of this approach and its complexity, first an exploratory trial is needed in order to evaluate the feasibility of this intervention package and possible trial procedures and to gain insights into potential mechanisms of change and impacts on patient-important outcomes. Trial results will have impacts on clinical research and practice: In the short term, results will (1) prove the feasibility of the intervention package and provide robust data about relevant context factors and required implementation strategies to be considered for a confirmatory evaluation of the skin care program’s clinical effectiveness and cost-effectiveness and (2) inform the protocol for subsequent confirmatory trials (e.g., in regard to the responsiveness of outcome measures and associated effect sizes, ICCs, and data collection methods).

This trial will benefit individual patients and aged nursing home residents in general. According to the latest systematic reviews and researching [2, 3], the skin conditions of interest are frequent in this population: In German long-term and geriatric care facilities, the PU prevalence is approximately 4% [43–45], the prevalence of dry skin is approximately 53% [46] and associated pruritus up to 14% [46, 47], and the prevalence of IAD ranges from 4% to 11% [48, 49]. The incidence and severity of these skin conditions will be reduced; thus, patient safety will be enhanced. The improvement of dry skin helps to prevent secondary infection and pruritus. Overall, QoL will be increased. Potential unhelpful care interventions will be avoided. Carefully developed and targeted skin care practice will reduce patients’ exposure to unnecessary and inappropriate products, thus reducing the risk of irritation, contact allergies, and other adverse effects [11]. In addition, so far, often neglected and overlooked age-related skin conditions , especially symptomatic xerosis cutis, which is an explicitly stated unmet need of aged patients [50], will be addressed.

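### The statement that the study is adequately powered for every variable does not carry over to pressure ulcers, nor to incontinence-associated dermatitis over the cited range: at the plan's own relative reduction, power is about 26% and 26–65%

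*Protocol article*

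**What the plan says.** The Sample size calculation section of the protocol article defines no primary outcome. It says the size was chosen so that the "power of statistical tests is sufficiently high for each of several binary and continuous outcomes under realistic assumptions". One binary scenario follows. It has 10 homes per arm ("If m = 10 nursing homes are included in each study arm"), about 23 residents per home after dropout, an ICC of 0.02 and an "incidence for the skin conditions of around p_C_ = 50% per annum", which the section converts to 29.3% in 6 months. Power exceeds 80% if the experimental figure is below 29.8% per annum (16.2% in 6 months). For continuous outcomes the detectable effect is d = 0.33. The section then concludes: "Since the effects of the experimental skin care regimen are expected to be larger, the study is not underpowered for each variable".

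Outcomes and measurements lists PU, IAD, intertrigo and skin tear incidence as separate main clinical outcomes, next to skin dryness, all measured at weeks 0, 12 and 24. Data management has the occurrence of these conditions recorded at the study visits. For German long-term and geriatric care, the Discussion reports that "the PU prevalence is approximately 4" per cent and that "the prevalence of IAD ranges from 4% to 11" per cent.

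**The concern.** One control risk, given without a source, stands for all the skin conditions, and the conclusion drawn from it covers each variable. Power for a fixed relative reduction drops steeply as the control risk drops, so a result at 29.3% says little about a condition with a point prevalence of 4%. The section also changes its event: the control arm has an incidence, while the experimental arm has a worsening of the skin condition. These need not be the same quantity.

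The trial's stated main aim is to give a basis for a confirmatory trial. A reader who accepts the power sentence could take a non-significant PU or IAD comparison as evidence of little effect when the comparison had little chance of showing one.

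**Working it through.** **Inputs.** From Sample size calculation: 10 homes per arm, 23 residents per home, ICC 0.02, two-sided α = 0.05, 29.3% v 16.2%. From Randomization and recruitment: 1:1 allocation. From the Discussion: PU prevalence about 4%, IAD 4–11%. From Outcomes and measurements and Data management: two follow-up examinations, with events recorded at visits.

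**Step 1: reproduce the plan's figure.**
- 6-month conversion: 1 − (1 − 0.50)^0.5 = 0.293 and 1 − (1 − 0.298)^0.5 = 0.162. Both agree.
- Design effect: 1 + (23 − 1) × 0.02 = 1.44. Effective n per arm: 230 / 1.44 = 159.7.
- Power = Φ[(|p_C − p_E| − 1.96·SE0) / SE1], with SE0 = √(2·p̄(1 − p̄)/n), SE1 = √([p_C(1 − p_C) + p_E(1 − p_E)]/n) and p̄ the mean of the two risks.
- For 0.293 v 0.162: SE0 = 0.0469, SE1 = 0.0463, (0.131 − 0.0919)/0.0463 = 0.84, power 80.0% (80.7% with unpooled variance).
- For d = 0.33, power is 79.6% with a t-test on 18 degrees of freedom and 83.6% with an individual-level t-test.

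The plan's calculations are therefore sound for the scenarios they describe.

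**Step 2: control risk implied by the cited prevalences.** If an event counts only when seen at week 12 or week 24, the share of residents ever seen with the condition cannot exceed the sum of the two point prevalences. New cases are fewer still, because residents affected at baseline are included in that sum.
- PU: at most 4% + 4% = 8%.
- IAD: at most 8% (2 × 4%) to 22% (2 × 11%).
- To reach 29.3% over two examinations, point prevalence would have to be at least 29.3/2 = 14.7%, about 3.7 times the cited PU figure.

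**Step 3: power at those risks, with the plan's own relative reduction.** Risk ratio = 0.162/0.293 = 0.553.

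| Control risk | Experimental risk | Power |
|---|---|---|
| 4% | 2.2% | 15% |
| 8% | 4.4% | 26% |
| 12% | 6.6% | 38% |
| 22% | 12.2% | 65% |
| 29.3% | 16.2% | 80% |

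For the 8% row: SE0 = 0.0270, SE1 = 0.0269, (0.0358 − 0.0529)/0.0269 = −0.64, and Φ(−0.64) = 26%.

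**Step 4: what 80% power would require.** Solving the same formula for the experimental risk gives about 1.4% at a control risk of 8% (a reduction of about 83%), about 10.5% at 22%, and 16.2% at 29.3%. At 4%, complete prevention gives only 73%. The plan's 13.1-point difference is larger than the whole 8% control risk.

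**The case against.** **No calculation is wrong.** This stands. Every figure in the section reproduces; the defect is the reach of the concluding sentence.

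**Larger effects are expected.** The section says so, but gives no size. At 8%, a halving of risk has 32% power, and about an 83% reduction is needed for 80%.

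**The 8% ceiling is conditional.** This also stands. The article gives no incidence for any single condition. Enrolled residents (aged 65 or more, care degree 2 or higher) may have higher prevalence than the cited settings. Participant timeline plans four visits while the outcomes section gives three measurement times, and the schedule figures are not available here. A third follow-up examination would raise the PU ceiling to 12% and power to 38%.

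The ceiling also disappears if events between visits are counted. With 4% prevalence and an assumed mean duration D of 1 to 3 months, 1 − exp(−6 × (0.04/0.96)/D) gives a 6-month PU risk of 22% to 8% and power of 65% to 26%. A much shorter duration would change this: at half a month the risk would be 39%. For IAD at 11% prevalence the same formula gives 52% at 1 month and 22% at 3 months, so at the upper end the plan's calculation could cover IAD. The documents point the other way, since occurrence is recorded at visits and the items listed for extraction from records under Baseline assessment concern PU risk and prevention, not PU occurrence.

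**The 50% may describe the conditions together.** Possibly, but it would then support no single condition, and the outcomes section defines no composite.

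**Stronger readings.** A reader might infer three further failures that the documents do not support:
- That quality of life and pain are underpowered because residents are split over several scales. The plan does use different instruments ("QoL in residents without cognitive impairment will be assessed with the WHO - Five Well-being Index"), but no proportions are given, so any loss of power would rest on an invented split.
- That calling the detectable effects relatively small is an error. On Cohen's scale, 29.3% v 16.2% is h = 1.144 − 0.829 = 0.32, in line with d = 0.33, so the description is defensible.
- That intertrigo and skin tears are also shown to be underpowered. The article gives no prevalence for either in this setting, so nothing is shown for them.

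**Conclusion.** The concern holds in limited form. The sentence claiming adequate power for each variable is not supported for PU, nor for IAD over the cited range. Power at the plan's own relative reduction is about 26% for PU (15% at a control risk of 4%, 38% at 12%) and 26–65% for IAD.

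This rests on two assumptions: prevalence in enrolled residents is near the cited values, and events count only when seen at the week 12 and 24 examinations. The second matters most, especially for IAD. Under the first, the plan's own numbers give no route to a 29.3% PU risk from two examinations.

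A reader might take this as a fault that undermines the trial. The documents do not support that: there is no primary outcome, all p values are exploratory, and estimating effect sizes and ICCs is an explicit objective. It is a correction to a stated power property, not to design or analysis.

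**What to change.** In Sample size calculation:

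1. Delete the clause that the study is not underpowered for each variable.
2. Limit the power statement to binary outcomes with a 6-month control risk near 29% and to continuous scores measured in all residents.
3. State the difference detectable with 80% power at lower control risks: 8% to about 1.4%; 22% to about 10.5%; 29.3% to 16.2%.
4. Say that the PU and IAD comparisons are for estimation with confidence intervals, and that a non-significant result is not evidence of no effect.
5. Use one event definition for both arms in place of incidence in one and worsening in the other, and say whether events between visits count.

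The cost is a few sentences and a less favourable stated power. No residents, visits or analyses are added.

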### Statistical analysis

All statistical evaluations will be conducted by using the statistical programming language R and IBM SPSS statistics (IBM Corporation, Armonk, NY, USA). Variables will be described at the cluster (nursing homes) and individual level on an intention-to-treat basis. A two-level analysis will be conducted for all outcomes. For comparisons of event rates in the control and experimental groups, we will use appropriate generalized mixed-effects models. Furthermore, for all outcomes, ICCs will be calculated providing a basis for future sample size estimation in a subsequent confirmatory trial. The two-sided level of significance is α = 0.05. All *p* values will be considered exploratory, no adjustment of the level of significance will be performed, and no interim analysis is planned. The data collected for process evaluation will be analyzed descriptively. The main aim of the trial is to provide a solid basis for a subsequent confirmatory trial.

### Analysis population

The statistical analysis will be run on the basis of the intention-to-treat principle. At the cluster level, the study population includes all nursing homes which have been randomly assigned. At the individual level, it contains all residents of the randomly assigned nursing homes who meet the inclusion criteria and who have passed the baseline visit. Nursing home residents who stay for longer than 2 months outside the nursing homes (e.g., due to hospital admission), die, or leave the nursing home during the study period will be analyzed until that time point (early termination).

### Data management

A paper case report form (pCRF) file will be created for the study. Data (informed consent process and consent retrieval; demographics; medical history; clinical examination; measurements of skin functional parameters; clinical scores; occurrence of PU, IAD, xerosis cutis, ST, and intertrigo; compliance; delivery and return of the skin care diary; and delivery of products if applicable) will be recorded in written form during the study visits. An electronic case report form (eCRF) will be developed by the Charité Coordinating Center for Clinical Trials at the Charité-Universitätsmedizin Berlin (KKSC). Data from the pCRF will be extracted and entered into an eCRF. Data management and handling of data will be conducted in accordance with the trial-specific data management plan and the International Conference on Harmonisation (ICH) guidelines.

Data entry will be performed by the trial site personnel. According to a pre-defined query process, changes to data entries in the eCRF (if any) will be made at the site by the qualified trial site personnel. The eCRF will have an audit trail with appropriate functionality for data capture, tracking, and documentation of any queries or changes. Electronic signatures will be used to verify the data and identify the person entering or changing the data.

#### Data monitoring

Monitoring of the study is the responsibility of the investigator and will be undertaken by an independent monitor from the KKSC. The monitor is responsible for reviewing the progress of the study and for verifying adherence to the protocol as well as compliance to ICH Good Clinical Practice and also for handling any problems that arise. The monitor will visit the center before, during, and after completion of the study to ensure that the study is conducted, recorded, and reported in accordance with the protocol.

#### Harms

This is neither a drug nor a medical device study. The used or provided skin care products (or both) may be regarded as cosmetic products according to EU Regulation Number 1223/2009 on cosmetic products. In addition, long-term care residents are affected by a variety of diseases and medical problems. Therefore, the terminology of undesirable effects and serious undesirable effects will be adopted for this trial and will be used for the documentation throughout the study.

## Discussion

To the best of our knowledge, this is the first trial implementing a comprehensive evidence-based skin care and prevention strategy in institutional long-term care. The skin care and prevention strategy was developed systematically, taking currently available evidence and expert opinion into account. Given the novelty of this approach and its complexity, first an exploratory trial is needed in order to evaluate the feasibility of this intervention package and possible trial procedures and to gain insights into potential mechanisms of change and impacts on patient-important outcomes. Trial results will have impacts on clinical research and practice: In the short term, results will (1) prove the feasibility of the intervention package and provide robust data about relevant context factors and required implementation strategies to be considered for a confirmatory evaluation of the skin care program’s clinical effectiveness and cost-effectiveness and (2) inform the protocol for subsequent confirmatory trials (e.g., in regard to the responsiveness of outcome measures and associated effect sizes, ICCs, and data collection methods).

This trial will benefit individual patients and aged nursing home residents in general. According to the latest systematic reviews and researching [2, 3], the skin conditions of interest are frequent in this population: In German long-term and geriatric care facilities, the PU prevalence is approximately 4% [43–45], the prevalence of dry skin is approximately 53% [46] and associated pruritus up to 14% [46, 47], and the prevalence of IAD ranges from 4% to 11% [48, 49]. The incidence and severity of these skin conditions will be reduced; thus, patient safety will be enhanced. The improvement of dry skin helps to prevent secondary infection and pruritus. Overall, QoL will be increased. Potential unhelpful care interventions will be avoided. Carefully developed and targeted skin care practice will reduce patients’ exposure to unnecessary and inappropriate products, thus reducing the risk of irritation, contact allergies, and other adverse effects [11]. In addition, so far, often neglected and overlooked age-related skin conditions , especially symptomatic xerosis cutis, which is an explicitly stated unmet need of aged patients [50], will be addressed.

Findings of this exploratory trial may lay the foundation for a change in the development of clinical standards and practices in general as it moves the perspective from focusing on individual conditions to a more comprehensive view on overlapping or coexisting health problems, in this case common skin conditions, in old-aged long-term care receivers. This helps to pool resources and to increase overall patient safety within health-care institutions and to increase professional competencies of nurses, who have the major responsibility in aged care.

## Trial status

This trial is registered at the German Clinical Trials Register and ClincialTrials.gov. The local ethics committee (EA1/243/18) approved the study on January 11, 2019. At the time of submission of this manuscript, the recruitment of the nursing homes had been started. The first 12 nursing homes expressed interest. Of them, six nursing homes committed to participation and were in preparation to start the study in April and June 2019. Six other nursing homes have confirmed appointments for the first information meetings.

## Abbreviations

eCRF: Electronic case report form
GDS: Global Deterioration Scale
IAD: Incontinence-associated dermatitis
ICC: Intra-class correlation coefficient
ICD: International Classification of Diseases
ICH: International Conference on Harmonisation
KKSC: Coordinating Centre for Clinical Trials at the Charité - Universitätsmedizin Berlin
NRF: Neues Rezeptur Formularium
ODS: Overall Dry Skin
pCRF: Paper case report form
PU: Pressure ulcer
QoL: Quality of life
QUALIDEM: (No original term, measurement instrument for proxy rating of quality of life in people with dementia)
SCH: Stratum corneum hydration
ST: Skin tear
TEWL: Transepidermal water loss
WHO: World Health Organization
